## Abstract

**Background:**

Many people living with epilepsy (PLWE) reside in rural communities, and epilepsy self-management may help address some of the gaps in epilepsy care for these communities. A prior randomized control trial of a remotely delivered, Web-based group format 12-week self-management program (SMART) conducted in Northeast Ohio, a primarily urban and suburban community, demonstrated improved outcomes in negative health events such as depression symptoms and quality of life. However, there is a paucity of research addressing the needs of PLWE in rural settings.

**Methods:**

The present study leverages collaboration between investigators from 2 mid-western US states (Ohio and Iowa) to replicate testing of the SMART intervention and prioritize delivery to PLWE in rural and semi-rural communities. In phase 1, investigators will refine the SMART program using input from community stakeholders. A Community Advisory Board will then be convened to help identify barriers to trial implementation and strategies to overcome barriers. In phase 2, the investigators will conduct a 6-month prospective randomized control trial of the SMART program compared to 6-month waitlist controls, with the primary outcome being changes in negative health events defined as seizure, self-harm attempt, emergency department visit, or hospitalization. Additional outcomes of interest include quality of life and physical and mental health functioning. The study will also assess process measures of program adopters and system end-users to inform future outreach, education, and self-management strategies for PLWE.

**Discussion:**

The method of this study employs lived experience of PLWE and those who provide care for PLWE in rural and underserved populations to refine a remotely delivered Web-based self-management program, to improve recruitment and retention, and to deliver the intervention. Pragmatic outcomes important to PLWE, payers, and policymakers will be assessed. This study will provide valuable insights on implementing future successful self-management programs.

**Trial registration:**

ClinicalTrials.gov NCT04705441. Registered on January 12, 2021

## Background

It is estimated that one in 26 Americans will develop epilepsy which remains associated with a high burden of medical complications, decreased quality of life, and premature mortality [1]. A growing body of research supports self-management approaches that can improve outcomes in people living with epilepsy (PLWE). However, because of diverse needs across various sub-populations and known health disparities, it is important to understand how evidence-based epilepsy self-management approaches might impact outcomes across a broad range of PLWE, including those living in rural and semi-rural communities.

While the literature on disparities in epilepsy is growing, comprehensive, comparative data remain limited [2], and most of the literature has not focused on the needs of rural communities. Twenty percent of the US population reside in rural communities, which tend to have a higher rate of poverty, depression, and suicide than urban communities [3, 4]. There has been a widening gap in healthcare outcomes referred to as the rural mortality penalty, resulting in over 134 excess deaths per 100,000 [5]. A survey of Midwestern neurologists identified low income, lack of insurance, transportation difficulties, stigma, and misperceptions about epilepsy as barriers interfering with epilepsy care in rural regions [6]. Residents of rural communities and other underserved communities may experience health disparities and have multiple areas of unmet need in epilepsy care. A recent targeted review on the social determinants of health in epilepsy recommended engaging patients, especially those from disadvantaged backgrounds, in self-management in order to educate and empower patients [7]. The Managing Epilepsy Well (MEW) Network has been a national leader in developing, testing, and disseminating evidence-based epilepsy self-management programs [8]. One of these, the self-management for people with epilepsy and a history of negative health events (SMART) program, developed by researchers at Case Western Reserve University (CWRU), is an online 12-week behavioral group format program targeted to reducing barriers and maximizing facilitators to self-care in high-risk people with epilepsy [9]. SMART has been demonstrated to reduce epilepsy-related complications and improve quality of life [10]. SMART is delivered by peer educators (patients with epilepsy) and nurse educators. Thus, SMART combines the portability and low cost of a Web-based intervention with the personally salient components of behavior modeling that can be obtained by interacting with individuals who have “walked the walk” in living with and coping with epilepsy.

A new SMART 2.0 research study is intended to (1) replicate efficacy findings of the original SMART randomized control trial (RCT) in an alternative setting (rural and semi-rural communities), (2) incorporate best practices and recommended strategies for enhancing study recruitment and retention, and (3) assess program adopter’s perceptions of the intervention to inform future implementation and dissemination. This report describes the methods of the planned replication study using a prospective 2-site, 6-month RCT design to assess SMART vs. 6-month waitlist (WL) control. The study will assess effects on epilepsy complications and other outcomes in a diverse sample with epilepsy including rural people with epilepsy. We hypothesize that at 6-month follow-up, SMART will be associated with reduced negative health events (NHEs) compared to WL. We also expect that SMART will be associated with improved quality of life, functioning, and physical and mental health.

## Methods

This 2-site, 2-phase study (Fig. 1) will investigate the effects of the SMART program on health outcomes in people with epilepsy who have had recent NHEs defined as a seizure, self-harm attempt, emergency department visit, or hospitalization within the last 6 months. The study will be conducted in Ohio and in Iowa, led by a team of researchers from CWRU in Cleveland and from the University of Iowa (UI) in Iowa City in collaboration with stakeholders in epilepsy and rural healthcare.

**Fig. 1 Fig1:**
[figure not shown]
Phase 1 and phase 2 study operationalization. NHE negative health event

### Phase 1

Phase 1 is intended to set the stage for a successful RCT that will inform future dissemination and implementation efforts should RCT findings be positive. Qualitative methods will be used to collect information from informed and committed local stakeholders. Two focus groups composed of PLWE and their family members from rural communities in Iowa and two focus groups composed of rural health providers, social services agency administrators/staff, or other professionals working in rural health will be convened to collect information on perceived barriers and facilitators to participation in an epilepsy self-management program, as well as impressions of the SMART self-management curriculum. Information obtained from these local stakeholders will also help the investigators to develop a robust recruitment strategy and a set of practices that will maximize engagement and retention of subjects. Focus groups will be conducted via Zoom technology, last 60–90 min, and use a semi-structured interview guide adapted from previous studies in self-management of neurological conditions conducted by the CWRU investigators [11, 12]. The total number of individuals in the focus groups will be in the range of 32–40 individuals, which is within the recommended sample size range for qualitative studies [13, 14].

### Community Advisory Board (CAB)

Building upon strong existing partnerships between members of the study team and epilepsy/neurological care partners across the states of Iowa and Ohio, the study team will obtain input from relevant community stakeholders to develop an a priori recruitment and retention strategy intended to maximize enrollment of typically hard-to-reach individuals with epilepsy from underserved and rural communities. The CAB will be composed of up to 16 individuals, including individuals with epilepsy, epilepsy specialists, clinicians, and administrators who practice in rural or underserved communities, and representatives from the Epilepsy Association/Epilepsy Foundation.

There will be 3 video-conference calls prior to the RCT. In the first call, CAB members will review the SMART curriculum and identify potential barriers to recruitment and retention. In the second meeting, CAB members will review the list of barriers and suggest solutions and strategies for reaching people with epilepsy who may not be initially help-seeking and discuss potential methods of retaining these individuals in the program once they are recruited. In the third CAB meeting, the list of strategies will be finalized, and the investigators will obtain input on how these strategies might be best operationalized.

### Phase 2

Phase 2 is a prospective 6-month comparative trial of SMART vs. WL in 160 individuals with epilepsy and a recent NHE. Participants will be randomly assigned (1:1 basis) to receive either SMART (*N* = 80) or WL (*N* = 80) using a computer-generated random number generator created in REDCap during the enrollment process. This is a simple randomization scheme together with permuted block randomization to insure similar treatment and waitlist group sizes. This randomization scheme is unavailable to study staff who enroll participants and assign to treatment or waitlist groups. The participants and nurse and peer educators are not blinded, due to the nature of the intervention. However, the data analysts have no interaction with participants or the nurse or peer educators. The investigators will conduct 8–10 separate and sequential SMART groups with up to 10 individuals in each group. SMART will consist of two main components: a 12-week remotely accessed “intensive” group format stage and a 12-week remotely accessed Web/telephone follow-up stage.

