### Setting and recruitment

To assess the potential of SMART to promote behavior change in people with epilepsy and NHEs, the investigators will build on their strong track record of working with local federal, state, and county entities that provide service to rural and underserved communities. At the Iowa site, study participants will be drawn from local clinical and community referral sources including the Epilepsy Foundation of Iowa and primary care networks. At the Ohio site, enrollment will emphasize recruitment outside of the Cleveland metropolitan area with assistance from the Epilepsy Association, Epilepsy Alliance of Ohio, and epilepsy care professionals affiliated with the University of Cincinnati. This will include advertisements and brochures. We will also obtain HIPAA Waivers of Authorization from the relevant IRBs at the recruiting sites so that we may identify and contact potential subjects. Since SMART is an adjunct to ongoing neurological and medical care, it is expected that study participants will continue to receive services with their regular medical clinicians and providers at all sites.

Participants will have a self-reported diagnosis of epilepsy, be at least 18 years of age, have experienced an NHE within the last 6 months, and be able to provide written informed consent and participate in study procedures. Study entry criteria are purposely broad in order to best represent “real world” people with epilepsy [15]. Actively suicidal/homicidal individuals and those with dementia will be excluded, as will pregnant women who are likely to need different and more intensive treatments.

The study team will attempt to oversample PLWE who live in rural or semi-rural settings. Classification of rurality will be determined based upon the 2013 Rural-Urban Continuum Codes [16], a classification scheme that distinguishes metropolitan counties by the population size of their metro area and nonmetropolitan counties by degree of urbanization and adjacency to a metro area. The official Office of Management and Budget metro and non-metro categories have been subdivided into 3 metro and 6 non-metro categories. Each county in the USA is assigned 1 of the 9 codes.

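### The allocation is called both simple and permuted block, and the primary tests ignore site and rurality: a loss of efficiency, not a bias

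*Protocol article*

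**What the plan says.** The Phase 2 section gives the ratio, "Participants will be randomly assigned (1:1 basis) to receive either SMART" or waitlist with 80 per arm, and then the scheme: "This is a simple randomization scheme together with permuted block randomization to insure similar treatment and waitlist group sizes". The only purpose stated is "to insure similar treatment and waitlist group sizes". Neither site nor rurality is mentioned as a stratification factor.

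Elsewhere the article gives both factors some weight:
- Methods: "The study will be conducted in Ohio and in Iowa". Setting and recruitment lists different referral sources for each state.
- Setting and recruitment: "The study team will attempt to oversample PLWE who live in rural or semi-rural settings", and "Classification of rurality will be determined based upon the 2013 Rural-Urban Continuum Codes", which assign every county to one of nine classes, three metro and six non-metro.
- Background: one aim is to "replicate efficacy findings of the original SMART randomized control trial (RCT) in an alternative setting (rural and semi-rural communities").

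The hypothesis itself is an overall comparison: "We hypothesize that at 6-month follow-up, SMART will be associated with reduced negative health events (NHEs) compared to WL".

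The Data analysis section tests the proportion with a reduction in negative health events (NHEs) by Fisher's exact test, and the change in NHE count by the Wilcoxon-Mann-Whitney test. Study site and rural/urban status appear there only as explanatory variables in mixed models labelled exploratory.

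**The concern.** Simple randomization places no restriction on the sequence of assignments, whereas permuted blocks do. One allocation list cannot be both, and a reader cannot tell which was built. The choice affects how close the arm sizes will be and how predictable the next assignment is, in a trial whose participants and educators are not blinded.

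The second part concerns precision. Iowa and Ohio recruit through different channels, rural residents are to be oversampled, and the plan lists both factors as possible explanations of NHE outcomes. If either predicts outcome, primary tests that ignore it forgo precision that the trial's own data could supply. Without stratified allocation, a visible chance difference in site or rural mix is also fairly likely at this sample size. It would draw questions that the primary analysis, as planned, cannot answer.

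**Working it through.** **Inputs from the article.** 160 participants, 80 per arm, 1:1; 20% attrition, leaving 160 x 0.80 = 128, or 64 per arm; two-sided 5%; stated power 86% (Fisher) and 89% (Wilcoxon-Mann-Whitney).

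**Inputs assumed, because the article gives none.** Share of participants holding the factor, 30-50%; waitlist rates of NHE reduction within strata; a true difference of 27 points.

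**1. The plan's own figure.** The 64 per arm reproduces. The 86% cannot be reproduced, because the two proportions are not stated. Inverting exact Fisher power at 64 per arm, 86% corresponds to a difference of about 22 to 28 points for waitlist rates of 10% to 70% (22.8 points at 10%, 28.1 at 40%, 21.8 at 70%). An assumed 27 points is therefore in keeping with the plan.

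**2. Do the two named schemes differ in substance?** Under simple randomization the size of one arm is Binomial(160, 0.5).
- P(exactly 80/80) = 6.3%
- P(arm sizes differ by 10 or more) = 48%
- P(arm sizes differ by 20 or more) = 13%

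Permuted blocks hold the difference to about half a block, so only blocks serve the stated purpose.

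**3. Chance imbalance if allocation is unstratified.** With K of 160 participants holding the factor, the number X in one arm of 80 is hypergeometric, and the difference in share is |2X - K|/80.

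| Share assumed | K | 10 points or more | 15 or more | 20 or more |
|---|---|---|---|---|
| 30% | 48 | 22.7% | 5.7% | 0.9% |
| 50% | 80 | 26.8% | 8.2% | 1.7% |

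A normal tail without continuity correction, using SD = sqrt(2p(1-p)/80) = 7.2 to 7.9 points, gives 17-21% and 4-6% for the first two columns. That is too low, because the difference moves in steps of 2.5 points.

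**4. Type I error and power, proportion outcome.** Simulation with 20,000 runs, 64 per arm, one binary factor held by 50%, comparing Fisher with a Cochran-Mantel-Haenszel (CMH) test over the factor. Power at a 27-point difference:

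| Waitlist rate in the two strata | Unstratified, Fisher | Stratified, Fisher | Unstratified, CMH | Stratified, CMH |
|---|---|---|---|---|
| 40% / 40% (not prognostic) | 82.5% | 82.9% | 86.5% | 86.7% |
| 30% / 50% (moderate) | 82.5% | 83.2% | 88.3% | 88.9% |
| 20% / 60% (strong) | 81.7% | 84.7% | 92.4% | 92.9% |

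With no true difference, Fisher without stratified allocation rejects in 3.2-3.7% of runs and CMH in 4.6-5.0%.

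Stratifying allocation while keeping Fisher adds 0.4, 0.7 and 3.0 points. Moving to CMH without touching the allocation adds 86.5 - 82.5 = 4.0, 88.3 - 82.5 = 5.8 and 92.4 - 81.7 = 10.7 points. The 4.0 points in the first row arise with no prognostic factor at all, so they reflect only Fisher's conservatism.

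With four site-by-rurality strata, the design proposed here, CMH gives about 87-91% against 82-85% for Fisher, a gain of about 3-8 points, with CMH type I error near 5%. The 10.7-point figure needs one factor with a 40-point prognostic gap and should be read as an upper extreme.

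The gain for the NHE count outcome was not computed.

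**The case against.** The best reply is that the allocation sentence is loose and not wrong. If simple is read as unstratified, the sentence describes ordinary permuted blocks, and both the stated purpose and the 80/80 target point that way. This largely stands: the wording is an editorial fault, although it should still name one scheme.

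Four stronger readings are tempting, and the documents do not support them.
- *That the trial is known to be unstratified.* The article mentions no stratification but does not rule it out. It is a condensed account, and Trial status refers to a protocol version that is not shown. The imbalance figures are therefore conditional.
- *That the primary comparison is biased or invalid.* Chance imbalance is already part of the error of a randomized comparison. Type I error stays below 5%, and gaps of 20 points or more occur in only 1-2% of trials. A 10-point imbalance in a factor with an assumed 20-point prognostic gap moves the estimate by 0.10 x 20 = 2 points, against the 22-28 points that the power statement implies.
- *That site and rurality define the study question.* Rurality is the setting and an oversampling aim, and site is neither. No primary contrast by either is planned.
- *That a rural estimate is materially weakened.* With 48 rural participants (30% of 160, assumed), a 20/28 split has variance factor 1/20 + 1/28 = 0.0857, against 1/24 + 1/24 = 0.0833 for an even split, about 3% more.

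It can also be said that the Primary outcome section names a binary mixed model, which could carry covariates. But Data analysis calls those models exploratory and assigns the primary comparison to Fisher's test. That conflict is a separate matter, and it leaves adjustment of the primary analysis unclear at best.

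**Conclusion.** The point holds as a modest, inexpensive improvement. Two statements rest on the text alone: one sentence gives two names to the allocation scheme, and the primary tests in Data analysis leave out two covariates that the trial already collects. The rest is a matter of efficiency. Stratified allocation alone is worth about 0-3 points of power, and a stratified primary test of the proportion about 3-8 points with or without it. The size rests on assumed factor shares, waitlist rates and a 27-point effect, and part of the gain would appear even if site and rurality predicted nothing.

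**What to change.** 1. Replace the allocation sentence with one scheme, permuted blocks, and say whether it is stratified and by what.
2. If allocation has not begun, stratify at least by site. If it has begun, leave the list alone; the analysis change below captures most of the gain.
3. Make the primary analyses stratified by site and metro/non-metro status, using the split already built into the county codes: a Cochran-Mantel-Haenszel test for the proportion with reduced NHEs and a van Elteren test for the change in NHE count. Keep the unadjusted Fisher and Wilcoxon-Mann-Whitney tests as sensitivity analyses, and fix this before any outcome data by arm are seen.

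Cost: the 86% and 89% in Sample size calculations were computed for the unadjusted tests and must be restated for the stratified ones, with the assumed proportions given. County of residence has to be recorded at enrolment. Some of the four strata may be small, depending on how well rural recruitment goes, so a rule for merging sparse strata should be set in advance.

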### Data analysis

Descriptive analyses will compare the individuals assigned to SMART or WL using Student’s *T*-test, Fisher’s exact test, and non-parametric tests when appropriate. The primary outcome is whether there is a difference in the proportion of individuals with reductions in the total number of NHEs in the prior 6 months, at baseline, and at follow-up (6 months after randomization) between SMART and WL, compared using a Fisher’s exact test. We will also test for the difference in NHE counts between baseline and follow-up using a non-parametric Wilcoxon-Mann-Whitney test (the distribution of this measure is expected to be non-normal based on our prior experience). Exploratory longitudinal mixed models with a subject-level random effect will be conducted to investigate a binary variable of no NHEs versus at least one NHE and for a count measure of total NHEs from baseline to 10 and 24 weeks. Explanatory variables will include study site, age, gender, race/ethnicity, number of seizure medications, rural/urban continuum status, and attendance or deviations from the study protocol. Analysis will be performed for the intention-to-treat population (all participants enrolled to receive the SMART trial), for the safety population (all participants who received any portion of the SMART intervention), and for the per-protocol population (all participants who completed the SMART intervention). There will be a delay between randomization and baseline assessments for individuals enrolled for both the SMART trial and the waitlist, which may vary based on the recruitment time required for cohorts and the number of cohorts that can be accommodated at one time. Every effort will be made to insure steady recruitment and sufficient numbers of cohorts to accommodate those recruited. In addition, the specific cohorts will be able to be identified for analysis, and if we find marked variability between the cohorts or the delay in starting the intervention, this will be addressed by the data monitoring committee.

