### Sample size calculations

Psychosocial interventions can reduce seizures and emergency department visits in people with poorly controlled epilepsy [34, 35]. Oosterhuis noted a 50% reduction in seizures with group psychoeducation [36]. In our original SMART efficacy trial, a total number of past 6-month NHEs were reduced by > 50%. The projected sample size is 160, with 80 subjects per arm. While the Web and phone-based access format of SMART optimized study retention and attrition rate in the original RCT was 14.2%, we conservatively assume 20% attrition at 6 months (*N* = 128). A 2-sided, 2-sample, Fisher’s exact test with a type I error of 5% will have 86% power to replicate the difference in the proportion of individuals with NHE reductions. For the second primary outcome which has a Laplace distribution, a 2-sided, 2-sample, Wilcoxon-Mann-Whitney test with a type I error of 5% will have 89% power to replicate the difference in NHE counts in the prior 6 months.

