## Trial status

We used protocol version 2 from July 2, 2020, and anticipate starting recruitment for the clinical trial in April of 2021 and completing recruitment by the end of 2023.

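### Participants are randomized at enrollment but wait for a SMART group to open, and the protocol times the 6-month visit on two incompatible clocks; if the clock is randomization, most of the SMART arm would be short of the full programme at the primary endpoint

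*Protocol article*

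**What the plan says.** - **Allocation** (Methods, Phase 2): participants are assigned 1:1 "using a computer-generated random number generator created in REDCap during the enrollment process", so each person is allocated on entry and not when a group is ready.
- **Delivery** (Phase 2): there are to be 8–10 "separate and sequential SMART groups with up to 10 individuals in each group". The programme comprises "a 12-week remotely accessed “intensive” group format stage and a 12-week remotely accessed Web/telephone follow-up stage", 24 weeks in all. The Experimental intervention section allows the group stage to take 10–12 weeks, so the total could be about 22 weeks.
- **Accrual** (Trial status): the investigators "anticipate starting recruitment for the clinical trial in April of 2021 and completing recruitment by the end of 2023".
- **Randomization clock**: Outcomes and analysis schedules the 13-week and 6-month assessments from randomization. The primary comparison in Data analysis is made "at follow-up (6 months after randomization) between SMART and WL".
- **Baseline clock**: Data analysis also announces a delay between randomization and baseline in both arms, "which may vary based on the recruitment time required for cohorts and the number of cohorts that can be accommodated at one time". Its second paragraph runs the 13-week event window from baseline and equates that window with the group sessions.
- **No anchor**: the Primary outcome section places the endpoint at week 24 of the trial without naming a starting date.
- **Power** (Sample size calculations): with 20% attrition, Fisher's exact test "will have 86% power to replicate the difference in the proportion of individuals with NHE reductions"; the second primary outcome is given 89%.

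**The concern.** A person allocated to SMART cannot start until a group opens. If the 6-month visit is counted from randomization, a 24-week programme leaves about two weeks for that wait. Any longer wait is usual-care time, the same as the waitlist receives, yet it counts in the SMART arm's outcome because events are counted over the preceding 6 months. The protocol expects most of the reduction after the group sessions end, so a late start removes mainly the period in which the effect is expected.

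If the visit is instead counted from a baseline taken when the group opens, exposure is intact. Baseline is then measured a variable time after allocation, when unblinded participants know their arm. Mixing the two origins is worse: with baseline at group start and the 6-month visit timed from randomization, the two 6-month look-back periods overlap by the length of the wait. Visits, look-back periods and the primary comparison therefore all depend on which origin applies.

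**Working it through.** **Inputs.** 80 SMART participants (Phase 2); 8–10 groups of up to 10, hence 10 groups of 8 or 8 groups of 10. These hold 80–100 people, which fits the SMART arm alone. Recruitment runs from April 2021 to the end of 2023, or 33 months (33 × 52.18/12 = 143.5 weeks). Programme 24 weeks, or 22 with a 10-week group stage. Endpoint at 6 months (26 to 26.1 weeks) or week 24.

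**Wait for a group.** These figures assume even accrual, one group filling at a time and a start when full.
- SMART accrual: 80/33 = 2.42 per month, one person every 143.5/80 = 1.79 weeks.
- Fill time: 8 × 1.79 = 14.3 weeks; 10 × 1.79 = 17.9 weeks.
- Mean wait, (k − 1)/2 × 1.79: 3.5 × 1.79 = 6.3 weeks for k = 8; 4.5 × 1.79 = 8.1 weeks for k = 10.

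**Slack on the randomization clock.** 26.1 − 24 = 2.1 weeks.

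**Share of the SMART arm not finished at the endpoint (randomization clock).**

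| Programme / endpoint | Wait model | Unfinished |
|---|---|---|
| 24 wk / 26 wk | evenly spaced arrivals | 6/8 = 75% to 8/10 = 80% |
| 24 wk / 26 wk | random arrivals (simulated) | 73–79% |
| 24 wk / 26 wk | uniform continuous wait | 1 − 2.1/14.3 = 85% to 1 − 2.0/17.9 = 89% |
| 22 wk / 26 wk | all three | 59–78% |
| 24 wk / week 24 | all three | 88–100% |

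**What is unfinished.** With evenly spaced arrivals and a 12-week group stage, the share still in the group stage at 26 weeks is 0% (groups of 8) to 20% (groups of 10). At week 24 it is 12.5–30%. The rest of the unfinished lack only late maintenance contacts.

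**Time after the group stage, within 26 weeks.** With no wait it is 26 − 12 = 14 weeks. Averaging max(0, 14 − wait) over the evenly spaced waits gives 7.7 weeks (55%) for groups of 8 and 6.2 weeks (44%) for groups of 10.

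**Baseline clock.** If baseline is taken at group start and the 6-month visit is counted from it, waiting removes no exposure and leaves nobody unfinished.

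**Power.** The evaluable number reproduces: 160 × 0.8 = 128, or 64 per arm. The 86% does not, because no proportions are stated. Inverting the exact Fisher power at 64 per arm, with waitlist proportions assumed at 0.2–0.6, gives a difference of about 25–28 percentage points. Shrinking that difference by an assumed amount gives:

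| Assumed dilution | Fisher power |
|---|---|
| 10% | 76–78% |
| 20% | 63–68% |
| 30% | 50–56% |

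**The case against.** The strongest reply is that the protocol admits the delay, places it before baseline in both arms and ties the 13-week window to baseline and to the group sessions. On that reading nothing is lost. The visit table, which might settle the anchor, is not visible in the text at hand. This stands in part: the randomization reading cannot be treated as established. But the baseline rule is written only for the 13-week event window. For the 6-month visit, the assessment schedule and the primary-analysis sentence both name randomization.

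A second reply is that the protocol promises steady recruitment and enough cohorts, and refers marked variability in the delay to the data monitoring committee. These measures bear on the length and spread of the wait, but they fix no limit, and a similar average delay in every cohort would not trigger the referral.

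Third, those counted as unfinished mostly miss maintenance contacts of at most 15 minutes. That is correct, and it limits the finding. The cut in time after the group stage remains.

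Fourth, comparing arms as assigned, with waiting included, is a legitimate question, and dilution runs toward no difference. That also stands, provided the protocol says so.

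A reader might infer that some 85–88% of the SMART arm will certainly be in mid-programme at the endpoint, and that true power is nearer 50% than 86%. The documents support neither. The percentage belongs to one wait model on one of two clocks. The power figure needs proportions, a dilution factor and the earlier trial's timing, none of which is given. If the earlier trial had the same wait, the stated power stands.

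**Conclusion.** The point holds as a conflict over time origin with a material consequence on one branch. The document times the 6-month visit from randomization while placing an unspecified cohort delay between randomization and baseline and counting the 13-week window from baseline.

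- **Randomization as origin:** a mean wait of about 6–8 weeks against about 2 weeks of slack leaves most of the SMART arm (about 60–100% across the variants) without the full programme. At 26 weeks at least 80% would have finished the group stage. Mean time after it falls from 14 to about 6–8 weeks.
- **Group-start baseline as origin:** no exposure is lost, but baseline follows randomization by a variable interval.

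The waits assume even or random accrual over 33 months and groups filling one at a time. Starting smaller groups more often would shorten them; groups filled separately by site would lengthen them. The effect on power has a clear direction on the randomization clock if the earlier trial had no such wait, but its size cannot be derived. This should be corrected; confidence is medium.

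**What to change.** Consent and screen continuously, but randomize in batches. When about 16–20 eligible participants are ready, with the sites pooled because delivery is remote, re-check eligibility, complete baseline, randomize the batch 1:1 and open its SMART group shortly afterwards. Date the 13-week and 6-month visits and the event look-back periods in both arms from that single date. Bring Outcomes and analysis, Primary outcome and Data analysis into line with it, including whether the endpoint is week 24 or 6 months. This serves both readings, because randomization, baseline and the start of SMART then nearly coincide.

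**Cost.** Protocol wording and a change to the REDCap set-up. At 160/33 = 4.85 participants per month, a batch of 16–20 takes 3.3–4.1 months to assemble, so some people wait before randomization instead of after it. Some may withdraw, or no longer have had an event within the last 6 months, and would need replacing. This may slow recruitment, but losses before randomization do not bias the comparison and the analysis sample need not grow.

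**If individual randomization is kept.** State one time origin for every visit and look-back period. If it is randomization, say that the 6-month result includes waiting time and that the 86% and 89% assume no dilution from it.
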